### Participant Recruitment

Participant recruitment for each study phase will be facilitated by both face-to-face and online (eg, social media and email) approaches. Information posters will be placed across the GCHHS patient waiting areas containing the principal investigator’s (JP) contact details (email, phone number) and a questionnaire QR (quick response) code.

### Study Outline

First, approval for the study was gained from the Gold Coast Hospital and Health Service (GCHHS) HREC and the University of Canberra HREC.

#### Study Phase 1

Study phase 1 will consist of the development and piloting of the online Australian diabetes-specific QoL questionnaire. In all, 25-30 adults (≥18 years old) with T1DM will be included. Data will be collected via an online questionnaire (10-15 minutes) followed by a face-to-face or online interview (20-30 minutes), with the period of data collection lasting 1 month. The face-to-face or online interview location will be the Gold Coast University Hospital, Outpatient Department, Diabetes Resource Centre or the Zoom online platform (the participants may choose their preferred interview method), respectively. Interview data will be audio-recorded, transcribed verbatim, coded, and parsed for common themes. A summary of key suggestions for revising the online questionnaire to be used in study subphases 2a and 2b will be produced.

#### Study Phase 2

Study phase 2a will be the initial validation of the online Australian diabetes-specific QoL questionnaire. In all, 364 adults (≥18 years old) with T1DM will be included. Data will be collected via an online questionnaire (estimated completion time 10-12 minutes). Participants will have access to the questionnaire for 2 weeks. If the questionnaire link expires, the participant may request a new link by contacting JP. The data collection period for this phase will last 3 months.

Study phase 2b will consist of subsequent validation of the Australian diabetes-specific QoL questionnaire using the MOS SF-36, the DQOL, and the PAID-20 questionnaires. Three months after study subphase 2a is completed, study subphase 2b will commence. Participants from study subphase 2a will be invited by email to complete the same online questionnaire for a second time. In addition, they will be asked to complete the MOS SF-36 [52], DQOL [49], and the PAID-20 [53] questionnaires. Responses will be analyzed to determine the statistical reliability and validity of the Australian diabetes-specific QOL questionnaire. In all, 100 adults (≥18 years old) with T1DM will be included. Data will be collected via an online questionnaire (estimated completion time 15-18 minutes). Participants will have access to the questionnaire for 2 weeks. If the questionnaire link expires, the participant may request a new link by contacting JP. The data collection period for this phase will last 3 months.

#### Study Phase 3

Study phase 3 will comprise preintervention, intervention, and postintervention procedures. The overall aim of this phase is to determine if an association exists between a low carbohydrate diet, QoL, and glycemic control in adults living with T1DM through use of a cross-sectional cohort study. In all, 16-23 adults (≥18 years old) with T1DM will be included.

The preintervention period will begin 1 week prior to commencing the intervention procedure. Participants will attend the study hospital for approximately 3 hours to do the following: complete the study consent form (hard copy), if not already completed; discuss the intervention process ensuring they have a clear understanding of what is required during all phases of the intervention; receive an information kit containing the study procedure, the research team (endocrinologist [PD], credentialed diabetes educator [CDE; DI], and diabetes dietitian [JP]) and Gold Coast Hospital Emergency Department contact details, a food diary, a sick day management plan, and support services (in case any psychological distress is experienced during the study); complete the online Australian diabetes-specific QoL questionnaire; have weight (kg), height (cm), and glycated hemoglobin (HbA_1c_) recorded; receive continuous glucose monitoring system (CGMS) education and supply of CGMS equipment; apply the CGM sensor to their abdominal wall, attach the transmitter, and establish a connection between the transmitter and their own compatible smart device in order to enable recording and displaying of their glucose levels; and receive instruction on how to continue with their usual, daily routine, and be asked to commence recording what they eat and drink via a food diary. The day prior to commencing the intervention, participants will receive their individualized meal plans by email.

The intervention procedure will take place in the participants own environment and last 12 weeks. Participants will be expected to perform the following during the intervention period: follow the low carbohydrate dietary plan (dietary composition: 20% carbohydrate [<100 g], protein 25%, and fat 55%) as prescribed by a diabetes dietitian, complete a daily food diary, test blood ketone levels weekly (at fasting), participate in a weekly endocrinologist appointment to discuss blood glucose levels and insulin adjustments by telephone, attend the diabetes dietitian appointment by telephone to discuss any concerns with the dietary plan, contact DI if having problems with the CGMS, and change the CGM sensor every 10 days.

The postintervention procedure will begin the day after the intervention has been completed, and participants will attend the study hospital for up to 90 minutes for the following: to record weight (kg) and HbA_1c_ with DI, to complete the online diabetes-specific QoL questionnaire and online patient global impression change questionnaire, and to participate in a face-to-face CGMS experience interview with JP.

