Traditionally, it has been recommended that people living with T1DM consume 45% to 60% of total energy intake from carbohydrate sources [9]. Dietary approaches commonly used to manage glycemic control include carbohydrate counting, which matches insulin-to-carbohydrate intake, and/or a low glycemic index diet [10,11].

Recently, there has been a growing focus on the utility of a low carbohydrate diet to manage glycemic control in individuals living with T1DM [12,13]. This dietary management strategy has been thoroughly investigated in people living with type 2 diabetes mellitus (T2DM) [14,15]. However, there is a paucity of evidence regarding T1DM.

A very low carbohydrate diet is defined as 0-50 g per day or <10% of the total daily energy intake [16], while a low carbohydrate diet is defined as <130 g per day or <26% of the total daily energy intake [16,17]. Schmidt et al [12] conducted a randomized crossover study to examine the effects of a low carbohydrate diet (<100 g carbohydrate/day) compared to a high carbohydrate diet (>250 g carbohydrate/day) on glycemic control. Participant baseline characteristics included White adults from Denmark (male: 6/14, 43%; female: 8/14, 57%; 14 with T1DM; mean age 44 years, SD 12 years). Participant median diabetes duration was 19 (range 13-32) years, and the HbA_1c_ was 7.5% (range 7.2%-7.6%). Participants undertook two, 12-week interventions separated by a 12-week “washout” period, with 10 of the 14 participants completing the study. The study found that a low carbohydrate diet compared to a high carbohydrate diet did not significantly improve HbA_1c_, but did stabilize glucose variability and reduce hypoglycemia frequency (*P*<.001) [12].

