#### Study Phase 3: The Low Carbohydrate Dietary Intervention

A sample size of 16 has been calculated with a 0.05 significance level and power of 0.8 to detect a significant clinical difference of 1.0% in HbA_1c_. A 1.0% change in HbA_1c_ will be used because dietary changes alone have shown to improve HbA_1c_ by 1.0% [60]. To complete the study, 16 participants are required. To account for a 40% attrition rate [12], 23 participants will be the maximum number recruited.

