### Intervention Procedure

All participants will follow a prescribed meal plan to meet their estimated energy needs as per the Schofield formula [64]. Meal plan macronutrient distribution will be 20% carbohydrate, 25% protein, and 55% fat based on the Australian book, *The CSIRO Low Carb Diet* [65]. The meal plan contains no more than 100 g per day of dietary carbohydrate, making this intervention a low carbohydrate dietary regimen according to Feinman et al’s [16] 2015 definition. Alcohol influences blood glucose levels, food and fluid choices, and quantities consumed [66]. For this reason, participants will be strongly advised to abstain from alcohol consumption during the 12-week intervention. Weekly telephone follow-up will be conducted by JP to discuss any concerns or questions participants may have. Follow-up by telephone has been shown to be an effective method to monitor medical nutrition therapy [67,68]. Weekly telephone appointments will also be conducted by the research teams’ endocrinologist (PD) to discuss blood glucose level management and adjust insulin doses as needed.

Any hypoglycemia treatment will be recorded in the food diary and will detail when, what, and how much carbohydrate was used to treat the hypoglycemic event. If any hypoglycemic events occur, PD will discuss this with the participant during the weekly telephone appointment and advice will be provided to avoid future occurrences. Participants will check blood ketones once a week on the morning after an overnight fast to avoid diabetic ketoacidosis. If blood ketones are present (>0.6 mmol/l), participants will follow a “sick day” management plan, and, if unsure what to do, will contact PD for advice. Participants will be encouraged to follow their usual exercise habits, as no exercise advice will be given [69]. This study is unique, and if a participant feels they are unable to complete the 12-week intervention, they may withdraw at any time.

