### Postintervention Procedure

At the completion of the intervention, the participant’s weight (kg) will be recorded. An HbA_1c_ test will be performed by the research teams’ CDE (DI). The online Australian diabetes-specific QoL questionnaire will be readministered. An online patient global impression of change questionnaire will be administered to determine the participants’ perception of the degree of change following the intervention relating to glycemic control and QoL [70]. This questionnaire will consist of 2 questions using a 7-point scale (“no change/has got worse” to “a great deal better/considerable improvement”). Finally, in an individual interview, each participant will be asked 5 questions regarding the CGMS experience relating to its acceptability, perception, benefits, and barriers. An interview question guide will be used to facilitate the interview. Data will be transcribed, coded, and parsed for common themes for inclusion in a publication.

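### Phase 3 places its only follow-up HbA1c and QoL assessment at completion of the diet, so as written the primary outcomes would rest on completers and may overstate the benefit in those who start

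*Protocol article*

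**What the plan says.** The Phase 3 endpoint visit is described twice in the protocol article, both times by reference to finishing the diet. Study Outline (Study Phase 3) says "The postintervention procedure will begin the day after the intervention has been completed". Postintervention Procedure opens with "At the completion of the intervention, the participant’s weight (kg) will be recorded", then lists the HbA1c test, says "The online Australian diabetes-specific QoL questionnaire will be readministered", and adds the global impression of change questionnaire. No other post-baseline HbA1c or QoL assessment appears in the article.

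For people who do not finish, Intervention Procedure says only that "if a participant feels they are unable to complete the 12-week intervention, they may withdraw at any time". It does not describe an assessment at or after that point.

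The Phase 3 sample size is counted in completers: "To complete the study, 16 participants are required". It continues: "To account for a 40% attrition rate [12], 23 participants will be the maximum number recruited". The Introduction describes the study cited for that rate, a randomized crossover comparison of low and high carbohydrate diets, as ending "with 10 of the 14 participants completing the study".

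Under Outcomes, the association of the diet with glycemic control (3.1), its association with QoL (3.2) and the mediation question (3.3) are all primary. The Discussion lists selection bias at enrolment as a limitation. It does not mention attrition.

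**The concern.** Phase 3 is a single nonrandomized group, so its result is a before-after change in whoever returns for the final visit. If only completers return, the change describes people who could keep to the diet, not people who were asked to start it.

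The two groups may well differ, most obviously on QoL. The new questionnaire is meant to cover dietary well-being, and the Introduction criticizes an existing instrument for leaving out satisfaction with food intake. Dislike of the diet is therefore both a plausible reason for stopping and part of what is being measured.

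The Conclusions and Discussion say that the findings could warrant a dietary guideline, and the Discussion says that Phase 3 will inform a larger randomized trial. A result that holds only for completers would be a poor input to either if it were read as the result in all who start. An analysis plan can choose how to handle missing values, but it cannot recover an HbA1c or a questionnaire that was never collected.

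**Working it through.** **Inputs.** From Sample Size (Study Phase 3): 16 completers required, 40% attrition, at most 23 recruited, target difference 1.0% HbA1c. From the Introduction: 10 of 14 completed the crossover study, so 4/14 = 28.6% did not. The article gives no outcome for people who stop, so their HbA1c change is assumed and varied.

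**The plan's own figure of 23, and the loss it implies**

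- 16 / (1 − 0.40) = 26.7, so 27. Dividing by the retained fraction does not give 23.
- 16 × 1.40 = 22.4, so 23.
- 16 / (10/14) = 22.4, so 23.
- Obtaining 16 completers from 23 means losing 7, and 7/23 = 30%.

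The stated 40% therefore disagrees both with the source as described and with 23 recruits giving 16 completers. That is a separate matter for the sample size section. Here it means only that the loss should be carried as a range.

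- At 4/14: 23 × 0.286 = 6.6, about 7 without an endpoint (16.4 completers).
- At 40%: 23 × 0.40 = 9.2, about 9 without an endpoint (13.8 completers).

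**Completer result against the result in all starters**

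Let p be the proportion lost, C the mean fall in completers and S the mean fall in those who stop.

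- Mean fall in all starters = (1 − p) × C + p × S
- Overstatement by the completer result = p × (C − S)

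With C set at 1.0% (the plan's target difference, used for illustration):

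| Assumed S | All starters, p = 40% | Overstatement | All starters, p = 4/14 | Overstatement |
|---|---|---|---|---|
| 0 | 0.60 | 0.40 | 0.71 | 0.29 |
| 0.5 | 0.80 | 0.20 | 0.86 | 0.14 |
| 1.0 | 1.00 | 0 | 1.00 | 0 |
| 1.25 | 1.10 | −0.10 | 1.07 | −0.07 |

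For example, at p = 40% and S = 0, the mean in all starters is 0.6 × 1.0 + 0.4 × 0 = 0.60 and the overstatement is 0.4 × (1.0 − 0) = 0.40 points.

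No comparable figure can be given for QoL, because the article states no expected change for the new questionnaire.

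**The case against.** The strongest reply is that this is silence in a condensed article. The two descriptions of the visit say when it happens for someone who follows the schedule. The sentence on withdrawal states a participant's right. A reader might infer that people who stop the diet are removed from the study and excluded from analysis, but no sentence says so, and no analysis set is defined. Follow-up after stopping and the handling of missing data may be set out in a full protocol or analysis plan that is not shown.

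This stands in part: exclusion cannot be stated as fact. However, the article does more than stay silent. It fixes the assessment at completion in two places, and its sample size counts completers and allows for attrition, which makes sense only if those who leave are expected to contribute no endpoint.

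A second reply concerns direction. A reader might infer that the completer result is bound to exaggerate the benefit. The documents do not support that, since they give no outcomes for people who stop. Someone who stops because of hypoglycemia, which the article lists as a potential adverse event, need not have a worse HbA1c. This reply stands fully, so the claim is limited to what may happen.

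Third, Phase 3 is called a pilot, the guideline language is conditional, and without a control group even the change in all starters would not isolate the effect of the diet. That limits what is at stake. It does not remove the gap between completers and starters.

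**Conclusion.** The point holds in a limited form. As the article is written, the Phase 3 HbA1c and QoL outcomes would rest on people who complete the 12-week diet, and they may overstate the benefit in those who start it.

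- **Extent:** about 7 to 9 of 23 without an endpoint. Neither end is firm. The 40% conflicts with the plan's other figures, and the 29% comes from a study of two 12-week periods with a 12-week washout, which may not match attrition here.
- **Size for HbA1c:** if completers fall by 1.0% and those who stop by 0 to 0.5%, the overstatement is 0.14 to 0.29 points at 29% loss and 0.2 to 0.4 points at 40% loss. Both changes are assumptions.
- **Direction:** the bias vanishes if those who stop do equally well and reverses if they do better. Data from completers alone could not show which case applies.

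It is worth acting on before Phase 3 enrolls because the remedy is cheap and a measurement that was never taken cannot be restored.

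**What to change.** State in the protocol and consent form that stopping the diet and withdrawing consent are different events. Invite everyone who starts the diet and stops early to the same assessment at 12 weeks: HbA1c on the same analyzer as at baseline, weight, the QoL questionnaire and the global impression of change. If someone declines to attend, offer the online questionnaires by link. The right to withdraw and the clinical management of participants stay as they are.

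Report the change in all starters with a 12-week measurement alongside the completer result, and state how many were not measured. If those who stop are not measured, limit the conclusions to completers. An HbA1c from the hospital record may differ in method and date from the study measurement, and it may not exist for participants recruited online, so use it only in a sensitivity analysis.

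The cost is new wording and one visit of up to 90 minutes for about 7 to 9 people, with no new staff. Some will decline, and the reported effect may be smaller. If a fuller document already provides for this follow-up, one sentence in the article saying so would settle the point.

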### Participant Eligibility Criteria

#### Inclusion Criteria

Study participants for each phase will self-identify against the following eligibility criteria: aged ≥18 years, living with T1DM, and T1DM diagnosis for ≥1 year. Study phase 3 includes 5 additional eligibility criteria that participants must meet: (1) use of multiple daily injections for insulin administration, (2) experience of at least one hypoglycemic episode since diagnosis, (3) knowledge of hypoglycemic management, (4) ability to test for blood ketones, and (5) knowledge of blood ketone management. 

#### Exclusion Criteria

Ineligible participants will include the following: people living with T2DM; people living with gestational diabetes mellitus; people who administer insulin using a continuous subcutaneous insulin infusion; those living with a known food allergy; those with a history of an eating disorder; those with a BMI <18.5 kg/m^2^; those aged <18 years; those who are pregnant or planning to conceive; those taking prescription medications, such as phentermine or corticosteroids; individuals with an active medical problem, such as a recent myocardial infarction, stroke or peripheral revascularization (within 3 months), active treatment of diabetic retinopathy, or recent serious infection (requiring in-hospital treatment or prolonged antibiotic therapy), that may hinder their ability to take part or may potentially affect study outcomes; those for whom written materials may be unsuitable (eg, vision-impaired or illiterate individuals); those unable to understand English; and those who fail to sign the participant consent form.

### Sample Size

#### Study Phase 1: Online Australian Diabetes-Specific QoL Questionnaire Development and Piloting

Sample size data will be collected from approximately 25-30 adult participants with T1DM. This sample size is based on previous research [54] and has been deemed as sufficient to facilitate in-depth face-to-face interviews [55].

#### Study Phase 2: Online Australian Diabetes-Specific QoL Questionnaire Validation

This phase will include 2 subphases: 2a and 2b. Subphase 2a will involve initial validation. This will include the online Australian diabetes-specific QoL questionnaire and will require 364 adult participants with T1DM. This sample size has been calculated using the participant-to-item ratio method [56]. Subphase 2b will involve subsequent validation. This will include the online Australian diabetes-specific QoL, MOS SF-36, DQOL, and PAID-20 questionnaires, and will require 100 responses to be collected for test–retest, convergent, and divergent validity statistical analysis. This sample size is based on biostatistician advice and other studies that have validated QoL instruments [49,57-59].

#### Study Phase 3: The Low Carbohydrate Dietary Intervention

A sample size of 16 has been calculated with a 0.05 significance level and power of 0.8 to detect a significant clinical difference of 1.0% in HbA_1c_. A 1.0% change in HbA_1c_ will be used because dietary changes alone have shown to improve HbA_1c_ by 1.0% [60]. To complete the study, 16 participants are required. To account for a 40% attrition rate [12], 23 participants will be the maximum number recruited.

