## Discussion

This study is the first of its kind to examine the association between a low carbohydrate diet, QoL, and glycemic control. This cross-sectional study protocol aims to develop, pilot, and validate a diabetes-specific QoL questionnaire and determine if an association exists between QoL and glycemic control while using a low carbohydrate dietary intervention in Australian adults living with T1DM.

The strengths of this study are that, to our knowledge, no previous published research has evaluated a low carbohydrate diet and its influence on QoL and glycemic control in Australian adults living with T1DM. Moreover, this is the first study to develop and validate an Australian T1DM-specific QoL questionnaire Therefore, the strengths of this study are its unique approach.

The potential limitations of this study include the fact that, first, the Australian diabetes-specific QoL questionnaire is not available to those who are vision impaired, intellectually impaired, or have any other type of diabetes, such as T2DM and gestational diabetes mellitus. Future studies could develop resources to include these populations. Second, in study phases 1 and 2, questionnaire data will be self-reported and may have the potential to produce social desirability bias [73]. However, using self-reported data is the most feasible option for this pilot study in order for the sample size (N=364) and statistical validation of the questionnaire to be achieved. Third, study phase 3 has been designed as a nonrandomized intervention group pilot study that will inform the design and feasibility of a potential larger randomized control trial. Finally, in study phase 3, there is potential selection bias: individuals who are highly motivated to improve glycemic control are more likely to participate [25].

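### Phase 3's 16 completers, 40% attrition and maximum of 23 recruits do not fit together, and 40% is not the attrition the protocol reports for the study it cites

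*Protocol article*

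**What the plan says.** The Phase 3 paragraph under Sample Size in the protocol article gives a conventional power statement: "A sample size of 16 has been calculated with a 0.05 significance level and power of 0.8", with the target "to detect a significant clinical difference of 1.0% in HbA_1c". It makes clear that 16 is a number of completers: "To complete the study, 16 participants are required". The allowance for loss follows: "To account for a 40% attrition rate [12], 23 participants will be the maximum number recruited".

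The resulting range appears again under Study Outline, Study Phase 3 ("In all, 16-23 adults (≥18 years old) with T1DM will be included") and in the Abstract.

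Reference 12 is described in the Introduction: a randomized crossover of a low against a high carbohydrate diet, in two 12-week periods with a 12-week washout between them, "with 10 of the 14 participants completing the study".

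**The concern.** The required number of completers, the attrition rate and the recruitment maximum are tied by one equation, so any two of them fix the third. Here the three stated values do not satisfy it. The source given for the rate, as this article itself reports it, also implies a different rate. At least one planning figure is therefore wrong as printed.

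At stake is whether the stated power of 0.8 goes with the stated recruitment. The Discussion adds a second reason to get this right: "study phase 3 has been designed as a nonrandomized intervention group pilot study" intended to inform a possible larger randomized trial. Retention is one of the inputs such a trial takes from its pilot, so a wrong rate, or a wrong way of inflating for it, could be carried forward.

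**Working it through.** **Inputs.** From Sample Size, Phase 3: 16 completers, significance level 0.05, power 0.8, difference 1.0% HbA1c, attrition 40%, maximum 23. From the Introduction: 10 of 14 completed the cited study. Not stated: the SD of the change, the test, and whether it is one- or two-sided.

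**1. Reproducing 23.** The standard inflation is N/(1 − d).
- With d = 0.40: 16/0.60 = 26.7, so 27. The stated 23 is not reproduced.
- Multiplying by (1 + d) instead: 16 × 1.40 = 22.4, so 23.
- With the cited study's own completion fraction: 16/(10/14) = 22.4, so 23.

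The last two agree because 14/10 = 1.4. Four dropouts per 10 completers is 4/10 = 40%, whereas attrition among those who started is 4/14 = 28.6%. The printed 40% looks like the first ratio labelled as the second. How the slip arose is inference; that the two sections disagree is not.

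**2. Completers from 23 recruits.**
- At 40%: 23 × 0.60 = 13.8, about 14.
- At 28.6%: 23 × 10/14 = 16.4.
- Largest loss that still leaves 16: 7/23 = 30.4%.
- Recruits needed at 40%: 26 × 0.6 = 15.6 falls short; 27 × 0.6 = 16.2 is enough.

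If dropouts are independent, the chance that at least 16 of 23 finish is 0.24 at 40% and 0.68 at 28.6%.

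**3. Power at 14 completers.** The 16 itself cannot be checked without an SD. So assume a two-sided paired t-test at 0.05 with power exactly 0.80 at n = 16. Solving the noncentral t (noncentrality d√n, n − 1 degrees of freedom) gives a standardized effect d = 0.749, which means an SD of change of 1.0/0.749 = 1.33% HbA1c. Holding d fixed:

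| Completers | Power |
|---|---|
| 16 | 0.80 |
| 15 | 0.77 |
| 14 | 0.74 |
| 13 | 0.70 |

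Other assumptions at n = 14:

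| Assumption | Power at n = 14 |
|---|---|
| Normal approximation, two-sided | 0.746 |
| t, one-sided | 0.747 |
| Normal approximation, one-sided | 0.752 |
| 16 rounded up from just above 15 (t, two- or one-sided) | up to 0.77 |

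The range is about 0.74 to 0.77.

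**The case against.** The strongest reply is that 23 is the right number. It is what the cited study's completion fraction yields, so the only error may be a mislabelled percentage with no consequence for recruitment or power. That largely stands, and it is why this point does not claim that Phase 3 is underpowered. A reader might infer that from the 40%, but it follows only if 40% is the intended planning rate. What remains is that the paragraph states 40%, and at 40% the number is wrong.

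A second reply is that 0.74 is not a figure from the document. That is correct. It rests on a test and an SD the article does not give, and Table 4 lists ANOVA, correlations and hierarchical regression. It is therefore shown as a range with its assumptions.

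Third, this is a small nonrandomized pilot, and an article condenses its full protocol. But the article chose to state a formal power calculation, and the problem is a stated figure that conflicts with others, not an omission.

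Fourth, the cited crossover was longer than the single 12-week period planned here, so its attrition may not carry over. That is fair. It bears on which rate to plan with, and does not reconcile the rate printed.

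A reader might also infer a bias from analysing completers only, because final measurement is tied to the end of the diet ("The postintervention procedure will begin the day after the intervention has been completed") and participants may withdraw at any time. The article does not support that as a finding. It nowhere says that people who stop the diet go unmeasured, or that only completers are analysed, and an article may leave both matters to the full protocol or analysis plan.

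**Conclusion.** The inconsistency is certain and needs nothing beyond the article. At 40% attrition, 16 completers require 27 recruits, four more than the stated maximum, and 23 recruits would yield about 14. The 40% also contradicts the article's own account of its source, which lost 28.6%. At that rate 23 is adequate.

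The practical size depends on which figure is wrong. If it is the rate, which is the more natural reading, one percentage changes and expected completers stay at about 16. If 40% is intended, the plan is about two completers short and power is about 0.74, at most 0.77, instead of 0.80. Those power figures assume a t-test on paired change with about 0.80 power at n = 16.

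**What to change.** Choose one of the following and say which.

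- **If the rate comes from the cited study:** restate attrition as about 29% (4 of 14) and keep 23. This costs one corrected figure and changes nothing in recruitment.
- **If 40% is a deliberate planning rate:** remove its attribution to the cited study, give the actual reason for it, and state that 23 recruits give about 14 expected completers, with the power at that number (about 0.74 under the assumptions above; the authors can compute it from their own SD and test). This costs one or two sentences and a less favourable stated power. Holding 16 completers at 40% would instead mean a maximum of 27, four more participants, with the 16–23 range amended in the Abstract, Study Outline and Sample Size.

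In either case, adding the SD of change, the test and the sidedness behind the 16 would let a reader verify the calculation, at the cost of one clause.
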